Nutritional support in the neonatal period is one of the basic conditions for survival of preterm children. Preterm children born in advance for various reasons need parenteml nutrition if enteral nutrition cannot meet their needs for growth and development. Although parenteral nutrition supplement can meet the temporary nutritional needs of preterm children, long-term parenteral nutrition has brought a series of problems, such as difficulties in peripheral venous puncture, susceptibility to complication by infections after central venous catheterization, parenteral nutrition-associated cholestasis (PNAC) and other complications. The ultimate goal of nutritional support in preterm children is to not only reach the normal growth speed of normal fetuses of similar gestational age in utero, but also have similar composition and function to normal fetuses. The ideal growth rate of preterm/low-birth-weight children during the neonatal intensive care unit (NICU) stay, by referring to the growth rate of normal fetuses in utero [13], is required as follows: average daily weight gain of 15 g/kg, weekly body length growth of 1 cm and weekly head circumference growth of 0.5–1 cm. However, preterm children after birth are faced with respiratory, digestive and other problems. For preterm children with various immaturely developed systems, how to solve the conflict between the high nutritional demands and low gastrointestinal tolerability of preterm children is a very realistic and important issue. Therefore, we need an appropriate early enteral nutrition management strategy for preterm children, although there is already a lot of consensus [14, 15], such as breastfeeding, initiation of microfeeding as early as possible, achieving full enteral nutrition as soon as possible, and shortening the time of parenteral nutrition in order to reduce complications. It is preferred to feed preterm children with their mothers’ breast milk [14], because such feeding can reduce the incidence of feeding intolerance, neonatal necrotizing enterocolitis (NEC), nosocomial infections, and growth and developmental retardation in preterm children [16]. In the event of inadequate supply of breast milk due to various reasons or inability of breastfeeding due to maternal diseases, breast milk provided by qualified breast milk donors becomes the second-best nutritional source for preterm children [17] During October 2010 to December 212, a multicenter double-blind controlled study conducted in Canada [18] found that the breast milk of donors was equally safe and effective as the breast milk of preterm children’s mothers, and after long-term follow-up and study, found that donor breastfeeding was favorable for the development of the nervous system in preterm children. In Taiwan, China [19], the breast milk in the breast milk bank is mainly used for feeding preterm children, infants with feeding intolerance and other infants suffering from metabolic disorders. Currently, many developed countries have established large breast milk banks, and breast milk can be shared even via the Internet [20]. However, the breast milk in breast milk banks is mostly for full-term children, whose nutritional ingredients cannot meet the needs of growth and development of preterm children. Breast milk banks have not been set up in most areas of China, and no unified standard donor screening, breast milk collection, disinfection, preservation and feeding practices have been established. The rural population accounts for the majority in China. Rural areas and small cities lack the capacity to treat preterm children, so preterm children are often sent to NICU in large cities for hospitalization. Their homes are often far away from the hospital, and China’s NICUs are mostly accompany-free wards, so family members cannot participate in feeding and care. Besides, many mothers cannot breastfeed because of their illness, and thus, preterm children hospitalized in NICUs in China are mostly fed with formula.

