#### Randomization and blinding

Randomization will be conducted by a researcher not involved in the recruitment and treatment of the participants. Concealed allocation will be performed using a set of random numbers placed in sealed opaque envelopes. The participants who meet the eligibility criteria will be divided into two groups by the physicians on duty via opening the envelopes. Reference to similar study literature is made for randomization [28, 31]. As extensively hydrolyzed milk protein formula and preterm children’s formula are greatly different in color and smell, physicians and nurses can easily distinguish these two formulae. Therefore, the study has chosen single-blinding, which means that only the participants and their guardians are unaware of the milk type.

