### Study design and outcomes

#### Outcomes

The first endpoint variable is the rate of food intolerance in preterm children. The second endpoint variables include (1) time to achieve full enteral nutrition; (2) time of parenteral nutrition; (3) time of NICU stay; (4) meconium drainage time; (5) daily spontaneous fecal discharge conditions; (6) growth and development conditions during the NICU stay and within 3 months after discharge, including daily weight growth rate, weekly body length growth rate and weekly head circumference growth rate; (7) different plasma parameter indicators before discharge from the NICU (total protein (TP), albumin, calcium (Ca), phosphorus (P), and alkaline phosphatase (ALP)). Other endpoint variables include the incidences of neonatal necrotizing enterocolitis, cholestasis, parenteral nutrition-associated cholestasis and congenital hypothyroidism (CH).

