
Children in line with any of the following six criteria can be diagnosed with feeding intolerance:Gastric residual liquid >50 % of the amount of previous feedingVomiting ≥3 times/day, or the vomitus is bile-likeGastric residual liquid or vomitus is bile-like or coffee grounds-likeAbdominal distension (abdominal girth is increased by ≥1.5 cm within 24 hours, with intestinal type), and abdominal distension caused by the use of nCPAP should be ruled outRequired fasting >2 mealsBlood in the stool or fecal occult blood positive, but it is required to rule out NEC based on the general conditions, blood indicators and abdominal X-ray examination of children

Clinical treatments:Amount of gastric residue: for children with tube feeding, draw the residual milk in the stomach every time before feeding.If birth weight is <1500 g, and gastric residue is <2 ml or if birth weight is ≥1500 g and gastric residue is <3 ml or gastric residue is <30 % of the amount of previous feeding, continue feeding and closely observe.If gastric residue is 30–50 % of the amount of previous feed, reduce the amount of feeding.If gastric residue is >50 % of the amount of previous feeding, fast for one meal, and continue feeding by the original feeding plan after the condition is improved.If there is bile-like or coffee grounds-like liquid in the gastric residual liquid or vomitus, stop feeding.Abdominal distension: measure the abdominal girth at fixed parts every time before feeding. If the abdominal girth is increased by ≥1.5 cm, reduce the amount of feeding or fast for one meal, and continue feeding by the original feeding plan after the abdominal distension condition is improved.If daily vomiting occurs >3 times, do not increase the milk volume or reduce the amount of feeding.In the event of blood in the stool or fecal occult blood positive, stop feeding.2.Diagnostic and treatment reference criteria for necrotizing enterocolitis (NEC) [50] are shown in Table 3.

**Table 3 Tab3:** Modified Bell staging criteria for neonatal necrotising enterocolitis

Staging	Systemic symptoms	Gastrointestinal symptoms	Radiological signs	Treatment
IA Suspected NEC	Temperature instability, apnoea, bradycardia, lethargy	Gastric retention, mild abdominal distension, fecal occult blood positive	Normal or intestinal dilation, mild ileus	Absolute fasting, gastric decompression, antibiotic therapy for 3 days, waiting for pathogen culture results

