### Sample size justification

We calculate the sample size based on the chi-square test comparison of the food intolerance rate during NICU between groups. Our previous pilot study shows that the rate of food intolerance during NICU for control patients is about 85 %. We expect that the intervention group will have a reduced intolerance rate to be 75 %. With these assumptions, we will need 148 infants in each group to finish the NICU part of the study to reach 80 % power and 5 % Type I error rate. Assuming that the dropout rate to be 20 %, we will need to enroll 185 infants in each group.

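### Staff who know the formula contribute judgement to the primary event, including a criterion that is their own fasting decision, and the protocol describes no arm-masked scoring

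*Protocol article*

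**What the plan says.** Under Randomization and blinding, the protocol explains that the formulae differ in color and smell, so that "physicians and nurses can easily distinguish these two formulae". It therefore chooses single-blinding, in which "only the participants and their guardians are unaware of the milk type". The blinded parties are newborns and their families. The Background says of Chinese NICUs, most of which do not admit accompanying relatives, "so family members cannot participate in feeding and care".

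Under Outcomes: "The first endpoint variable is the rate of food intolerance in preterm children". The definition is under Stage I: "Children in line with any of the following six criteria can be diagnosed with feeding intolerance". In short, the six are:

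1. gastric residual above half the previous feed;
2. vomiting at least three times a day, or bile-like vomitus;
3. bile-like or coffee-grounds residual or vomitus;
4. a girth rise of at least 1.5 cm in 24 hours with intestinal type, after ruling out distension from nCPAP;
5. fasting needed for more than two meals;
6. visible or occult blood in the stool, after ruling out NEC.

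The treatment rules in the same section leave some room over fasting. For a girth rise, staff may "reduce the amount of feeding or fast for one meal", and normal feeding resumes once the condition has improved, with no threshold given for improvement. The primary analysis is a chi-square test of the two rates.

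**The concern.** Criterion 5 turns a care decision into an outcome event, and the people who take that decision know the arm. Criteria 4 and 6 also need judgement: whether intestinal type is present, whether nCPAP explains the distension, and whether NEC is excluded. The protocol states its expectation openly. The Background says the hydrolyzed formula will speed transit and so reduce intolerance, and the Discussion says the results will confirm that it is safe and effective. If staff who share that expectation lean, even slightly, towards fasting or diagnosing control infants, the recorded rates separate without any formula effect. Neither the chi-square test nor the covariate-adjusted logistic model can tell that separation from a true one.

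**Working it through.** **Inputs.** From Sample size justification: "the rate of food intolerance during NICU for control patients is about 85" %, and "We expect that the intervention group will have a reduced intolerance rate to be 75" %; 148 evaluable infants per group; 20 % dropout; 185 enrolled per group; 80 % power; 5 % type I error. Sidedness is not stated, so two-sided is taken. The size of any ascertainment difference is not in the documents. It is an assumption, shown as a range.

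**The plan's own figure.** The dropout step reproduces: 148 / (1 − 0.20) = 185. The 148 does not. The usual formula gives n = [1.96·√(2·0.80·0.20) + 0.842·√(0.85·0.15 + 0.75·0.25)]² / 0.10² ≈ 250 per group two-sided (197 one-sided). That is a separate problem and nothing below depends on it. The figures use 148 and 185 because those are the planned numbers.

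**Bias calculation.** Suppose the true rate is 85 % in both arms, but the hydrolyzed arm is recorded at 85 % − d. The probability of p<0.05 is the sum, over all pairs of counts (x, y), of Bin(x; n, 0.85) × Bin(y; n, 0.85 − d) for which the two-sided Pearson chi-square rejects, by exact enumeration.

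| d (points) | Infants per 148 | Share of hydrolyzed-arm events, d/85 | P(p<0.05), 148/arm | P(p<0.05), 185/arm |
|---|---|---|---|---|
| 0 | 0 | 0 | 5.1 % | 5.1 % |
| 1 | 1.5 | 1.2 % | 5.8 % | 5.9 % |
| 3 | 4.4 | 3.5 % | 10.9 % | 12.2 % |
| 5 | 7.4 | 5.9 % | 20.7 % | 24.3 % |
| 10 | 14.8 | 11.8 % | 58.0 % | 67.5 % |

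The last row is simply the power for 85 % against 75 %. To reach it by bias alone, about 15 of the 126 expected events (0.85 × 148 = 125.8) would have to go unrecorded in one arm.

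**How much fasting can add.** Setting the treatment rules beside the criteria:

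- Residual above 50 % (fast one meal) and bile-like or coffee-grounds fluid (stop feeding) are already events under criteria 1 and 3.
- Blood in the stool (stop feeding) is already an event under criterion 6, unless NEC is not ruled out. NEC itself is managed with absolute fasting, so criterion 5 may be what captures those infants.
- A girth rise of 1.5 cm permits fasting without the intestinal-type and nCPAP conditions of criterion 4. An infant who fails criterion 4 can still become an event if fasting continues beyond two meals.

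Fasting is therefore largely, but not wholly, redundant. The discretionary part is mainly the distension route.

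**Can events be scored without the bedside diagnosis?** The data-collection section lists residual volume and nature, vomiting counts and nature, and abdominal distension. For milk it lists daily totals, not the previous feed; distension, not girth in centimeters; and stool character and color, not the occult-blood result. Most of what a rule needs is listed, but not all.

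**The case against.** The best case for the plan is that bedside blinding is not feasible, that the single-blind design is disclosed with its reason, and that most criteria carry numerical or visible thresholds. Because any one event during the stay counts, losing a case means missing every qualifying event in that infant. Programmed derivation and sensitivity analyses are also often left to an analysis plan, and that document is not shown. All of this stands, and it limits the point. It does not remove it: the protocol itself fixes who is blinded and makes a staff decision one of the criteria, and distinguishable formulae do not prevent scoring that is masked to arm. If the analysis plan already provides such scoring, the point is met.

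A reader might infer more than the text supports:

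- *That staff choose how often to look.* The protocol requires residuals to be drawn before every tube feed and girth to be measured before every feed. Feeding route is mostly set by gestational age and respiratory support, with discretion only for weak sucking and suspected reflux or slow emptying.
- *That modest judgement is enough to create the planned 10 points.* No misclassification rate is given, and 1 to 3 points raises the false-positive rate only to 5.8–10.9 % at 148 per arm.
- *That fasting should be removed from the primary event.* That is a debatable change to a definition taken from cited criteria. It could detach the endpoint from the pilot's 85 % and lose some infants with NEC.
- *That splitting results by gestational age would help.* It does not address blinding.
- *That families in this unit certainly take no part in care.* The Background remark describes Chinese NICUs in general.

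**Conclusion.** The point holds as an open route for ascertainment bias in the primary comparison, not as a demonstrated bias. Staff who know the arm contribute judgement to at least three of the six criteria, one of which is their own fasting decision, and the protocol describes no masked determination of the event. If there is no true effect and the control rate is 85 %, a recorded difference of 5 points, about 7 infants per arm of 148, would raise the chance of p<0.05 from about 5 % to 20.7 % (24.3 % at 185 per arm). At 1 point the effect is negligible. Where the trial would fall in that range cannot be read from the documents. The fasting criterion's own share is unknown and probably small, and reporting it would settle the matter. The remedy is cheap, so it is worth making before the data are analyzed.

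**What to change.** Keep the six-criterion endpoint and change how it is scored and checked:

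1. Derive each infant's event status by a fixed written rule, applied by program with the arm code masked, from the recorded bedside values and not from the bedside diagnosis.
2. Make sure the case form holds previous-feed volume, girth in centimeters and occult-blood result, which the data-collection section does not list.
3. Pre-specify, as the key sensitivity analysis, the primary comparison repeated without the fasting criterion. Report how many events in each arm rest on fasting alone, noting any infants with NEC among them.
4. State in advance that the efficacy claim will be tempered if the two analyses disagree.

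The cost is a few data fields and some programming. No additional assessor is needed and no clinical rule changes. The measurements and the fasting decisions would still be made by staff who know the formula, so bias at that level remains and should be stated as a limitation.

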#### Ethical aspects and informed consent

The study has passed the review of the Clinical Study Ethics Committee of Zhongda Hospital Southeast University, and the Ethics Committee’s approval number is 2014ZDSYLL115.0. Only the preterm children whose guardians give informed written consent will be included in this trial.

#### Study time

The study started in November 2014 and is expected to end in November 2017.

#### Interventions

The observation group is fed with extensively hydrolyzed milk protein (100 % whey protein) formula, while the control group is fed with preterm children’s formula until discharge from the NICU. After discharge, both groups are uniformly fed with ordinary formula (formula for 0 to 6-month-old infants).

### Study design and outcomes

#### Outcomes

The first endpoint variable is the rate of food intolerance in preterm children. The second endpoint variables include (1) time to achieve full enteral nutrition; (2) time of parenteral nutrition; (3) time of NICU stay; (4) meconium drainage time; (5) daily spontaneous fecal discharge conditions; (6) growth and development conditions during the NICU stay and within 3 months after discharge, including daily weight growth rate, weekly body length growth rate and weekly head circumference growth rate; (7) different plasma parameter indicators before discharge from the NICU (total protein (TP), albumin, calcium (Ca), phosphorus (P), and alkaline phosphatase (ALP)). Other endpoint variables include the incidences of neonatal necrotizing enterocolitis, cholestasis, parenteral nutrition-associated cholestasis and congenital hypothyroidism (CH).

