Incidence and outcome of feeding intolerance in preterm children, neonatal necrotizing enterocolitis, cholestasis, parenteral nutrition-associated cholestasis and congenital hypothyroidism3.Collection of enteral and parenteral nutrition and defecation conditions during the NICU stay:Milk opening time (h), total amount of daily milk (ml) and calories (kcal), total amount of daily parenteral nutrition (ml) and calories (kcal), total volume of daily fluids (ml) and total calories (kcal)The number of daily bowel movements, times of daily enema, trait and color of stool every time, meconium drainage time (h)Gastric residual volume (ml) and nature, times and nature of vomiting, and abdominal distensionTime to achieve full enteral nutrition (d), and total time of parenteral nutrition4.Collection of physical growth and development indicators during the NICU stay:Weight: weight will be measured at admission, once every day during hospital stay and before discharge with a baby electronic scale, and the data will be accurate to 10 g.Body length: body length will be measured at admission, once every week during hospital stay and before discharge, and the data will be accurate to 0.1 cm.Head circumference: head circumference will be measured at admission, once every week during hospital stay and before discharge, and the data will be accurate to 0.1 cm.5.Collection of laboratory indicators during the NICU stay:Daily monitoring of peripheral blood glucose and transcutaneous bilirubinWeekly detection of blood, liver and kidney function (total protein, albumin, total bilirubin, direct bilirubin, alkaline phosphatase, bile acids, alanine aminotransferase, aspartate aminotransferase, γ-glutamyl transferase, urea nitrogen, creatinine) and electrolytes (mainly calcium and phosphorus)Test of serum thyroid function 1–2 weeks after admission, including TSH, TT_3_, TT_4_, FT_3_ and FT_4_

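### The NEC endpoint sets no minimum Bell stage, so suspected cases that overlap with feeding intolerance can enter the count while in-hospital stage III cases are listed as an exclusion

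*Protocol article*

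**What the plan says.** **Endpoint.** The Outcomes section places NEC in a third tier, after the primary and secondary endpoints: "Other endpoint variables include the incidences of neonatal necrotizing enterocolitis". The section on data collected during the NICU stay is equally general: "Incidence and outcome of feeding intolerance in preterm children, neonatal necrotizing enterocolitis, cholestasis". Neither names a stage. The analysis section (Secondary outcome) compares comorbidity rates with Poisson models and does not split by stage.

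**Diagnosis.** Under Stage I: NICU stay, the article says "Diagnostic and treatment reference criteria for necrotizing enterocolitis (NEC) [50] are shown in Table 3". Table 3 is the modified Bell staging, from IA (suspected) to IIIB (advanced, perforated). The IA row reads:
- systemic signs: "Temperature instability, apnoea, bradycardia, lethargy";
- bowel signs: "Gastric retention, mild abdominal distension, fecal occult blood positive";
- imaging: "Normal or intestinal dilation, mild ileus";
- management: absolute fasting, among other measures.

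**Feeding intolerance (primary endpoint).** "Children in line with any of the following six criteria can be diagnosed with feeding intolerance". Criterion 1 is a gastric residual above 50 % of the previous feed. Criterion 4 is distension with a girth increase of at least 1.5 cm in 24 hours. Criterion 5 is a need to fast for more than two meals. Criterion 6 is visible or occult blood in the stool, with NEC to be ruled out from general condition, blood indicators and abdominal X-ray.

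**Other relevant text.** The exclusion criteria list stage III NEC during the hospital stay that requires transfer. Under Randomization and blinding, only participants and guardians are blinded; physicians and nurses can tell the formulae apart.

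**The concern.** Read together, the endpoint and its only diagnostic table admit suspected NEC as an event. Suspected NEC is the softest label in the table. It shares bowel signs with the primary endpoint, needs no radiological finding, and is applied by staff who know the allocation.

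Two things follow. First, a difference in the NEC count could reflect different labelling of intolerant infants and not different rates of proven disease. Second, a real difference in proven NEC could be diluted by suspected cases. The stage III exclusion adds to this: if those infants leave the analysis, the softest cases stay and the most severe ones go.

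This matters because the Background uses higher NEC rates on preterm formula than on human milk as part of the rationale, and the Discussion expects the results to confirm that the hydrolyzed formula is safe.

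**Working it through.** **Step 1. Compare the definitions.**

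| Stage IA in Table 3 | Feeding-intolerance criterion | Relation |
|---|---|---|
| Gastric retention | 1: residual > 50 % of previous feed | Same sign; IA has no numeric threshold |
| Mild distension | 4: girth up ≥ 1.5 cm in 24 h | Same sign; IA has no numeric threshold |
| Occult blood | 6: blood or occult blood, NEC ruled out | Same sign; criterion 6 carries a rule-out |
| Absolute fasting | 5: fasting > 2 meals | Appears to be met; no NEC rule-out |
| Temperature instability, apnoea, bradycardia, lethargy | none | Not an intolerance criterion |

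On criterion 5: initial feeds are given every two hours, so a third missed feed comes within about 3 × 2 = 6 hours. Table 3 does not say how long fasting lasts at IA, but it pairs it with 3 days of antibiotics while cultures are awaited. An infant handled as the IA row describes would thus be very likely to count as intolerant under criterion 5, even where criterion 6 is withheld because NEC is not ruled out.

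On the rule-out in criterion 6: the IA film may be normal, and Table 3 lists no blood abnormality before IIB. At IA the separation therefore rests on general condition.

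**Step 2. How much of the count could be suspected cases?** The documents give no NEC rate, so there is no stated NEC figure to reproduce. Inputs:
- intolerance 85 % (control) and 75 % (intervention), from Sample size justification;
- q, stage II NEC, the same in both arms: assumed 2 % to 5 %;
- f, the share of the other intolerant infants also labelled stage I: assumed, and varied;
- all stage II infants are taken to be among the intolerant, and stage III is left out.

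Control-arm NEC of any counted stage = q + f × (0.85 − q). Suspected share = f × (0.85 − q) / [q + f × (0.85 − q)]. Difference between arms = f × (0.85 − 0.75) = f × 10 points.

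| f | q | Control NEC count | Suspected share | Gap between arms |
|---|---|---|---|---|
| 1 % | 2 % | 0.02 + 0.0083 = 2.8 % | 29 % | 0.1 point |
| 1 % | 5 % | 0.05 + 0.0080 = 5.8 % | 14 % | 0.1 point |
| 10 % | 2 % | 0.02 + 0.083 = 10.3 % | 81 % | 1 point |
| 10 % | 5 % | 0.05 + 0.080 = 13.0 % | 62 % | 1 point |
| 50 % | 2 % | 0.02 + 0.415 = 43.5 % | 95 % | 5 points |
| 50 % | 5 % | 0.05 + 0.400 = 45.0 % | 89 % | 5 points |

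**Step 3. How much of the primary endpoint would be counted again?** Divide the control NEC count by 0.85. At f = 10 % this is 0.103/0.85 = 12 % to 0.130/0.85 = 15 % of intolerant infants. It passes half only at f of about 50 % (0.435/0.85 = 51 %).

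**Step 4. Dilution.** Suppose, as an assumption, that stage II NEC were 2 % on control and 5 % on the hydrolyzed formula, a ratio of 2.5. At f = 10 % the counts become 10.3 % and 0.05 + 0.10 × (0.75 − 0.05) = 12.0 %, a ratio of 12.0/10.3 = 1.17. The difference shrinks from 3.0 to 1.7 points.

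**The case against.** A good deal can be said on the other side.

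- **Silence is not a rule.** The article nowhere says that all stages count. A reader might infer that every Bell stage is included, but the stage III exclusion speaks against that, and Table 3 is a treatment reference as well as a diagnostic one. This stands: the fault is the missing floor, not a stated decision to count everything.
- **IA is not intolerance renamed.** A reader might infer that the two definitions coincide. They do not: criteria 1 and 4 have numeric thresholds, and IA has systemic signs that appear in none of the six criteria. This stands; the overlap is one of kind. The systemic signs separate the two less well than they might, because the discharge criteria (no apnoea, stable temperature) suggest that such signs are expected earlier in the stay.
- **Two labels for one infant are not an error.** Nothing makes intolerance and NEC mutually exclusive. This stands too, but criterion 6 withholds the intolerance label where NEC is not excluded and criterion 5 does not, so the two rules treat the same infant differently.
- **The endpoint is minor, and stages are a detail for fuller documents.** NEC is an other endpoint, never called a safety endpoint, and nothing is sized on it. That limits the weight of the point. It does not remove it, because the article itself supplies both the outcome and the table that defines it, and following them as written admits suspected cases.

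**Conclusion.** The point holds in a limited form. No minimum stage is set, the only reference starts at suspected disease, and unblinded clinicians apply the label. Suspected cases can therefore enter the NEC count and, at modest labelling rates, form most of it: about 14–29 % of the count at f = 1 % and 62–81 % at f = 10 %. These figures rest on assumed values of q and f, neither of which is in the documents.

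Two stronger readings are not supported. One is that NEC largely re-counts the primary endpoint: at f = 10 % only 12–15 % of intolerant infants would also be NEC cases. The other is that a spurious NEC benefit is likely: at f = 10 % the induced gap is 1 point, or about 0.01 × 148 = 1.5 infants per arm. The larger risks are dilution of a real difference in proven NEC and biased labelling, made worse if stage III cases drop out of the analysis.

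**What to change.** 1. Define the NEC endpoint as stage IIA or higher, counting stage III cases that occur after randomisation.
2. Record the Bell stage of every case. The data-collection section names incidence and outcome but not stage.
3. Tabulate IA and IB separately as suspected NEC, outside the NEC incidence.
4. Reconcile this with the exclusion criterion on in-hospital stage III NEC, so that such infants are not lost from the NEC count.
5. Reconcile feeding-intolerance criteria 5 and 6 with the IA row of Table 3, so that it is clear how an infant with suspected NEC is classified for the primary endpoint. How to do so is for the investigators, since any change there alters the primary endpoint.

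Items 1 to 3 concern counting and reporting, not care, and take a few lines and one data field. The price is fewer NEC events and a wider confidence interval for the difference.
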